## Abstract

**Background:**

Children commonly present to Emergency Departments (ED) with a non-blanching rash in the context of a feverish illness. While most have a self-limiting viral illness, this combination of features potentially represents invasive serious bacterial infection, including meningococcal septicaemia. A paucity of definitive diagnostic testing creates diagnostic uncertainty for clinicians; a safe approach mandates children without invasive disease are often admitted and treated with broad-spectrum antibiotics. Conversely, a cohort of children still experience significant mortality and morbidity due to late diagnosis. Current management is based on evidence which predates (i) the introduction of meningococcal B and C vaccines and (ii) availability of point of care testing (POCT) for procalcitonin (PCT) and *Neisseria meningitidis* DNA.

**Methods:**

This PiC study is a prospective diagnostic accuracy study evaluating (i) rapid POCT for PCT and *N. meningitidis* DNA and (ii) performance of existing clinical practice guidelines (CPG) for feverish children with non-blanching rash. All children presenting to the ED with a history of fever and non-blanching rash are eligible. Children are managed as normal, with detailed prospective collection of data pertinent to CPGs, and a throat swab and blood used for rapid POCT. The study is running over 2 years and aims to recruit 300 children.

Primary objective:Report on the diagnostic accuracy of POCT for (i) *N. meningitidis* DNA and (ii) PCT in the diagnosis of early MDReport on the diagnostic accuracy of POCT for *PCT* in the diagnosis of Invasive bacterial infection

Secondary objectives:Evaluate the performance accuracy of existing CPGsEvaluate cost-effectiveness of available diagnostic testing strategiesExplore views of (i) families and (ii) clinicians on research without prior consent using qualitative methodologyReport on the aetiology of NBRs in children with a feverish illness

**Discussion:**

The PiC study will provide important information for policy makers regarding the value of POCT and on the utility and cost of emerging diagnostic strategies. The study will also identify which elements of existing CPGs may merit inclusion in any future study to derive clinical decision rules for this population.

**Trial registration:**

NCT03378258. Retrospectively registered on December 19, 2017.

## Background

Early diagnosis of meningococcal disease (MD) is associated with improved outcomes including reduced morbidity and mortality [1, 2]. However during its prodrome phase invasive MD, which most often presents with a fever and non-blanching rash (NBR), is indistinguishable from many self-limiting viral infections, creating a significant diagnostic challenge for clinicians. This combination of features is a common presentation to Emergency Departments (ED) and inevitably leads to caution amongst clinicians, resulting in admission and administration of broad spectrum antibiotics to large numbers of children who do not have MD. Despite this cautious approach a cohort of children are still diagnosed late [1, 3]. Paediatric Emergency Research in the UK and Ireland (PERUKI, a research collaborative) highlighted these challenges in the context of a paucity of relevant evidence, and identified the derivation of a clinical decision rule (CDR) for the management of feverish children with NBRs as a priority for future research [4, 5].

## Current UK guidance

There are currently two clinical practice guidelines (CPG) in widespread use in the UK for the management of children with NBR. These are:National Institute for Health and Care Excellence (NICE) CG102 “Meningitis (bacterial) and meningococcal septicaemia in under 16s: recognition, diagnosis and management”The Newcastle-Birmingham-Liverpool algorithm [3, 6].

These CPGs were developed based on data collected prior to the introduction of Meningococcal vaccines into the UK vaccination schedule (Table 1) [6–9]. Both CPGs advocate a similar and cautious approach to management of non-blanching rashes in children. Both CPGs are reported to be highly sensitive for the diagnosis of MD (NICE 97%) and (NBL) 100% [6]. The specificity of the two CPGs has been estimated as 50% (NICE) 82% (NBL) [6]. The most significant difference between the two CPGs is that in the NBL CPG does not include fever or history of fever whereas the NICE CPG requires a fever (or history of fever) and NBR [6]. Data on sensitivity and specificity of the existing CPGs was collected largely before the introduction of meningococcal B and C vaccination meaning their performance in the current post vaccination era is unknown.

**Table 1 Tab1:** Current UK vaccination against invasive meningococcal disease

Current UK Vaccination Against Invasive Meningococcal Disease		
Vaccine (Serogroups)	Year Introduced into schedule	Age given
B	2015	8 weeks, 16 weeks, 1 year
C	1999	1 year^a^
ACWY	2015	14 years, University students 19–25 years

^a^Prior to 2016 meningococcal C vaccine was also administered at 12 weeks

### Point of care testing

Current guidance suggests a range of investigations aimed at establishing the risk of invasive disease, and/or identifying a pathogen. To date, these have predominantly been performed in laboratory settings. However recent advances in technology have created the potential for point of care testing to be employed, either to identify MD, or to stratify risk of invasive disease. The two which offer most promise in the context of NBR are Loop Mediated Isothermal Amplification for Meningococcal DNA (LAMP MD) and procalcitonin (PCT).

#### Lamp md

LAMP-MD is a rapid molecular amplification test for the detection of all serogroups of *N. meningitidis* DNA. It can be performed in the ED on a bench top analyser and provides results within 30 min (Fig. 1). Initial testing has shown that LAMP-MD has superior sensitivity (0.89 [95%CI 0.72–0.96]) and specificity (1.0 [95%CI 0.97–1.0]) in diagnosing MD than traditional tests (C-reactive protein [CRP] and White Blood Cell counts [WBC]) recommended by NICE [10, 11]. The LAMP-MD test is now available commercially and is CE-IVD approved. The test performs equally well on blood samples and throat swabs, [10] with results available more quickly from throat swabs due to a shorter and simpler DNA extraction process.

**Fig. 1 Fig1:**
[figure not shown]
Hibergene LAMP-MD testing equipment

#### Procalcitonin

Procalcitonin (PCT) is the precursor for calcitonin and is produced by parafollicular cells. It is a 116-amino acid protein that has roles in calcium metabolism. PCT is elevated during infection and typically rises within 2 h of the onset of a bacterial infection. A recently published meta-analysis of 6 studies, including 881 children, found PCT to be more sensitive (0.89 [95%CI 0.76–0.96]) and specific (0.74 [95%CI 0.4–0.92]) in diagnosing early MD than CRP or WBC [12]. A further strength of PCT is that it rises within 2 h of onset of bacterial illness and peaks at around 6 h (much earlier than CRP) [12]. ED clinical staff can perform PCT POCT on a bench top analyser with results available within 20 min. (Fig. 2)

**Fig. 2 Fig2:**
[figure not shown]
Samsung IB10 (BRAHMS) Procalcitonin

## Methods/design

As a diagnostic accuracy study our Petechiae in Children (PiC) study adheres to the STARD criteria for the reporting of diagnostic accuracy studies [13]. The gold standard test against which our outcomes are measured is quantitative PCR (qPCR) for *N. meningitidis* DNA in a sterile body site (blood or CSF). Or confirmation of an invasive bacterial infection through positive culture or qPCR of a bacterial pathogen.

### Study registration

The PiC study was registered at https://www.clinicaltrials.gov (trial registration: NCT03378258) on the 19th of December 2017. At the time of registration 24 patients had been recruited to the PiC study which opened on the 22nd of November 2017.

### Objectives

The co-primary outcomes are the diagnostic accuracy (sensitivity, specificity, positive predictive value, and negative predictive value) of:POCT for (i) *N. meningitidis* DNA and (ii) PCT in the diagnosis of MD in children with fever and NBRPOCT for *PCT* in the diagnosis of Invasive bacterial infection

Secondary objectives:Evaluate the performance accuracy of existing CPGs in identifying MDEvaluate cost-effectiveness of available diagnostic testing strategiesExplore views of (i) families and (ii) clinicians on research without prior consent (RWPC) using qualitative methodologyReport on the aetiology of NBRs in children with a feverish illness

### Study population and setting

#### Inclusion criteria

All children < 14 years of age attending the ED with reported or recorded fever (≥38 °C) and NBR.Unwell appearing children with features of meningococcal sepsis/meningitis as outlined in the National Institute for Health and Care Excellence (NICE) CG102 “Meningitis (bacterial) and meningococcal septicaemia in under 16s: recognition, diagnosis and management” [3].

#### Exclusion criteria

Children with pre-existing haematological conditions such as haematological malignancy, idiopathic thrombocytopenic purpura (ITP) and coagulopathy will be excluded.Existing Henoch-Schonlein purpura (HSP) under follow up

### Sample size justification

We have calculated that we need 203 test negative patients (negative LAMP & low procalcitonin) to estimate a negative predictive value (NPV) of 95% or greater with confidence intervals of +/− 3% (Calculation below). Disease prevalence is estimated at 15% or lower, based on preparatory work in our centre and other epidemiologic studies, and we anticipate a combined refusal of consent and dropout rate of 10%. We therefore aim to recruit a total of 300 patients to achieve this. We have chosen to focus on NPV because with possible MD the emphasis is on exclusion of a life-threatening infection and as such and test or CPG must have a high NPV.

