### NPV Calculation

Nnegative = Z_0.025_^2^x (NPV(1 ‐ NPV))/W^2 ^ = 1.96^2^x (0.95(1 ‐ 0.95))/0.03^2^ = 203

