### Statistical analysis

In keeping with the objectives we will report:

Primary:The diagnostic accuracy of POCT for (i) *N. meningitidis* DNA and (ii) PCT in the diagnosis of early MD against the reference standard (qPCR) for *N. meningitidis* DNA in blood/CSF). The sensitivity, specificity, NPV and PPV will be reported.The diagnostic accuracy of POCT for *PCT* in the diagnosis of early invasive bacterial infection against the reference standard of positive culture from a sterile site (blood/CSF). The sensitivity, specificity, NPV and PPV will be reported.

Secondary:The diagnostic accuracy of existing UK guidance in the diagnosis of early MD against the reference standard qPCR) of blood/CSF. The sensitivity, specificity, NPV and PPV will be reported. McNemar’s test will be performed to determine the significance in performance of different guidance. Where possible the effect of incorporating POCT into existing guidance will be explored and reported in term of sensitivity, specificity, NPV and PPV.Report on the aetiology of NBRs in children with a feverish illnessThe epidemiology of the population of children who present with fever and a NBR

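### The sample size rests on the NPV of LAMP and PCT combined, but the listed outcomes and analyses evaluate each test only on its own

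*Protocol article*

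**What the plan says.** In the protocol article, Sample size justification asks for "203 test negative patients (negative LAMP & low procalcitonin) to estimate a negative predictive value (NPV) of 95% or greater". The precision sought for that estimate is plus or minus 3 points. NPV Calculation gives the arithmetic: "1.96^2^x (0.95(1 ‐ 0.95))/0.03^2^ = 203". The sizing section also says "Disease prevalence is estimated at 15% or lower", allows 10% for refusal and dropout together, and arrives at 300.

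Objectives says: "The co-primary outcomes are the diagnostic accuracy (sensitivity, specificity, positive predictive value, and negative predictive value"), and applies these measures to three evaluations: LAMP for MD, PCT for MD, and PCT for invasive bacterial infection. The Abstract has the same three. Statistical analysis repeats them. Its first item takes LAMP as (i) and, as (ii), "PCT in the diagnosis of early MD against the reference standard (qPCR"); its second is PCT alone for invasive bacterial infection.

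The nearest item to a combination is secondary: "Where possible the effect of incorporating POCT into existing guidance will be explored".

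**The concern.** The group that fixes the sample size is defined by two results together, a negative LAMP and a low PCT. None of the listed outcomes or analyses is defined that way. The guideline item does not fill the gap: it is conditional, it is secondary, and it evaluates a guideline with point-of-care testing added, not the two tests as a rule of their own.

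Two things are at stake. First, the protocol says it chose NPV because the aim is to exclude a life-threatening infection, yet the rule it used for that purpose has no planned estimate, although all the data for it are collected. Second, a single statement of 203 negatives and plus or minus 3 points is left to stand for three rules whose negative groups differ in size.

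**Working it through.** **The plan's own figure.** With z = 1.96, NPV = 0.95 and W = 0.03, n = 1.96² × 0.95 × 0.05 / 0.03² = 202.75, rounded up to 203. The figure reproduces. The article does not show the step to 300. The simplest route is 203 / 0.85 = 238.8, then 238.8 / 0.90 = 265.4, i.e. 266, which 300 covers. That route treats every child without disease as test negative, so it takes specificity as 1.

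**Inputs for the check**
- LAMP sensitivity 0.89, specificity 1.0 (LAMP-MD paragraph of the background).
- PCT sensitivity 0.89, specificity 0.74, 95% CI for specificity 0.40 to 0.92 (Procalcitonin paragraph of the background). Assumption: these hold at the study's threshold of 1.93 ng/ml.
- Prevalence p = 0.15; evaluable children 300 × 0.90 = 270 (Sample size justification).
- Assumption: the two tests are independent given disease status. The pair, negative only if both are negative, then has sensitivity 1 − 0.11² = 0.9879 and specificity 1.0 × 0.74 = 0.74.

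**Formulas**
- Expected negatives = 270 × [(1 − p) × sp + p × (1 − se)].
- Expected NPV = (1 − p) × sp / [(1 − p) × sp + p × (1 − se)].
- Half-width at NPV 0.95 = 1.96 × √(0.0475 / negatives).
- Recruits needed for 203 negatives = 203 / (share negative) / 0.90.

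| Rule | Share negative | Negatives of 270 | Expected NPV | Half-width at NPV 0.95 | Recruits for 203 negatives |
|---|---|---|---|---|---|
| LAMP | 0.85 + 0.0165 = 0.8665 | 234.0 | 98.1% | 2.8 points | 261 |
| PCT | 0.629 + 0.0165 = 0.6455 | 174.3 | 97.4% | 3.2 points | 350 |
| Pair | 0.629 + 0.0018 = 0.6308 | 170.3 | 99.7% | 3.3 points | 358 |

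**Sensitivity of the 170**
- Prevalence: about 180 at 10% and 190 at 5%. Even at zero prevalence it is 270 × 0.74 = 199.8, still below 203.
- PCT specificity: 0.40 gives about 92 negatives and 0.92 gives about 212. At 15% prevalence, 203 negatives need a specificity of (203/270 − 0.0018) / 0.85 = 0.88, which lies inside the quoted interval.
- Independence: with LAMP specificity at 1.0, dependence matters only among diseased children. The both-negative count then lies between 270 × 0.629 = 169.8 and 169.8 + 270 × 0.15 × 0.11 = 174.3, so this assumption hardly moves the count. It does move the pair's NPV, which falls to 97.4% at the upper end.

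**Half-widths at each rule's own expected NPV**
- LAMP: 1.96 × √(0.981 × 0.019 / 234) = 1.7 points.
- PCT: 1.96 × √(0.974 × 0.026 / 174) = 2.4 points.
- Pair: 1.96 × √(0.997 × 0.003 / 170) = 0.8 points. This rests on only 170.3 × 0.0029 ≈ 0.5 expected missed cases, where the Wald form is unreliable, so read it only as small.

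**The case against.** The strongest reply is that sizing on the pair is conservative. A child negative on both tests is negative on each, so 203 both-negative children would guarantee at least 203 negatives for every single-test NPV listed. That is correct, and it rules out the reading that the sample size argument applies to no primary outcome. The article's accuracy figures do not, however, lead one to expect 203 such children.

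A second reply is that precision is adequate anyway. The target is an NPV of 95% or greater, so 0.95 is the least favourable value in that range, and at the expected NPVs all three half-widths are within 3 points. This also stands. A reader might infer from the shortfall of 170 against 203 that 300 is too few; the figures do not support that.

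Third, the bracket in Sample size justification might be meant test by test, and the closing sentence there, which speaks of what a test or guideline must achieve, lends this some support. The joint reading is the more natural one. On the other reading, PCT still yields about 174 negatives, not 203, so the passage needs rewording either way.

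Fourth, an analysis plan that is not shown could contain the joint table. So the most that can be said is that this document does not plan it; a reader should not infer that it will never be estimated. The article itself does fix both the sizing quantity and the outcomes, and these disagree. Nor is there much room for a data-driven choice of rule, since the bracket and the stated PCT threshold already define a negative result. What remains open is mainly the handling of invalid or missing results.

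**Conclusion.** The point holds as a mismatch between the quantity that justifies 300 and the quantities the article plans to report. No listed outcome becomes invalid.

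On the article's own figures about 170 both-negative children are expected where 203 are stated, a shortfall of about 33. At an NPV of 0.95 the half-width is 3.3 points against the stated 3. For the listed single tests it is 2.8 (LAMP) and 3.2 (PCT). The shortfall arises because the step from 203 to 300 appears to allow for prevalence and dropout but not for PCT specificity. It would vanish if that specificity were about 0.88 or higher.

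The count assumes that the cited PCT accuracy applies at the study threshold and that all 270 children have both results. The article allows for invalid LAMP results and for PCT being omitted when blood is short, but its 10% covers only refusal and dropout.

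One further gap is that the 15% is not tied to a condition. The rationale for choosing NPV points to MD, but the article does not say that the prevalence figure does.

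**What to change.** 1. In Statistical analysis, and in Objectives as a primary or key secondary outcome, add the NPV, sensitivity, specificity and PPV, each with a 95% CI, of the combined rule against the MD reference standard. Define negative as a valid negative LAMP with PCT not above the protocol's 1.93 ng/ml threshold, and positive as either test positive. It need not become a further co-primary outcome.
2. In Sample size justification, state which condition the 15% prevalence refers to.
3. In the same section, restate the expected number of negatives and the resulting precision for LAMP, PCT and the pair, allowing for specificity as well as prevalence.

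Alternatively, if no joint evaluation is intended, reword Sample size justification so that it refers to each single-test NPV, with the expected negatives and precision for each.

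The cost is one extra 2x2 table from data already collected, a few sentences, and a slightly less favourable stated precision.

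### At the planning NPV of 95%, 203 test-negative children give a confidence interval of about −4/+2.5 points, not the stated ±3

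*Protocol article*

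**What the plan says.** Under *Sample size justification*, the protocol article says that "we need 203 test negative patients (negative LAMP & low procalcitonin") in order "to estimate a negative predictive value (NPV) of 95% or greater with confidence intervals of" plus or minus 3%. NPV was chosen as the sizing quantity because "the emphasis is on exclusion of a life-threatening infection".

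The section *NPV Calculation* shows the source of 203: the squared normal quantile 1.96² times NPV(1 − NPV), divided by the squared half-width, with the numbers entered as "0.95(1 ‐ 0.95))/0.03" squared.

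The recruitment target of 300 rests on two further inputs: "Disease prevalence is estimated at 15% or lower", and "we anticipate a combined refusal of consent and dropout rate of 10"%.

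The *Statistical analysis* section lists NPV among the measures to be reported and names no interval method.

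**The concern.** The formula gives the half-width of a symmetric interval. For a proportion near 1 estimated from about 200 children, the confidence interval is not symmetric: its longer arm points down, away from 100%. A symmetric ±3 understates that arm and overstates the upper one.

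The lower arm is the one this study depends on. The article sizes on NPV because it wants to exclude a dangerous infection, so a reader will ask how low the true NPV could be. The printed statement suggests that an observed 95% comes with a lower limit near 92%. If the true figure is nearer 91%, the stated precision is too favourable on the side that bears on safety.

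**Working it through.** **Inputs.** NPV 0.95, half-width 0.03 and z = 1.96 (*NPV Calculation*); 203 test negatives, 300 recruits, prevalence 15% and losses 10% (*Sample size justification*).

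**1. The plan's own figure.** n = 1.96² × 0.95 × 0.05 / 0.03² = 202.75, rounded up to 203. It reproduces.

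**2. The interval at the planning value.** Ten missed cases among 203 is the whole-number result closest to 95%: 193/203 = 95.07%.

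- Normal approximation: 0.9507 ± 1.96 × √(0.9507 × 0.0493 / 203), giving 92.1% to 98.1%.
- Wilson: centre (p + z²/2n)/(1 + z²/n) = (0.9507 + 0.0095)/1.0189 = 0.9424. Half-width 1.96 × √(p(1 − p)/n + z²/4n²)/(1 + z²/n) = 0.0307. Interval 91.2% to 97.3%, arms −3.9/+2.2.
- Clopper-Pearson (beta quantiles): 91.1% to 97.6%, arms −3.9/+2.5.

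At exactly 95%, treating 0.95 × 203 as the count, the arms are −3.9/+2.3 (Wilson) and −4.0/+2.6 (exact).

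**3. Does the recruitment margin close the gap?** 300 × 0.90 × 0.85 = 229.5, about 230 test negatives. This assumes that every child without disease tests negative. At an NPV of 95% the lower arm is then 3.6 points (Wilson) or 3.7 (exact), so the gap narrows but remains. A lower arm of 3 points at 95% would need about 315 (Wilson) or 319 (exact) test negatives.

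**4. The rest of the stated range.** Lower arm of the exact interval, in points:

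| NPV | 203 test negatives | 230 test negatives |
|---|---|---|
| 95% | 4.0 | 3.7 |
| 97.4% | 3.2 | 3.0 |
| 98.1% | 3.0 | 2.7 |
| 99.7% | 2.1 | 1.9 |

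At 203 the lower arm reaches 3 points at an NPV of about 98% by either method.

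The three higher values are what the article's own accuracy figures imply. For LAMP-MD: "Initial testing has shown that LAMP-MD has superior sensitivity (0.89", with specificity 1.0. For procalcitonin: "found PCT to be more sensitive (0.89", with specificity 0.74. At 15% prevalence:

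- Procalcitonin alone: 0.74 × 0.85 / (0.74 × 0.85 + 0.11 × 0.15) = 0.629/0.6455 = 97.4%.
- LAMP-MD alone: 0.85/(0.85 + 0.0165) = 98.1%.
- Both negative, misses independent: 0.629/(0.629 + 0.15 × 0.11²) = 99.7%. If both tests miss the same children, it is 97.4%.

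**5. Lower limits for small counts, exact, n = 203.** With 0, 1, 2 or 4 missed cases: 98.2%, 97.3%, 96.5% or 95.0%.

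**The case against.** The strongest reply is that ±3 is close to right as an average half-width and that planning at 95% is cautious. Both parts have substance. The mean of the two arms at 95% is 3.1 points (Wilson) or 3.3 (exact), so the interval is mainly shifted down rather than much wider. Precision also improves as NPV rises, and the article's own accuracy figures point to values above 95%. Neither part rescues the printed statement: it is made for 95%, the lower arm there is about 4 points, and an average of the arms does not help when only one of them bears on exclusion.

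Two stronger readings should be resisted.

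- A reader might infer that the reported intervals will be badly wrong. The normal-approximation interval does perform poorly near 100%: at n = 203 its coverage is 93.6% at an NPV of 95% and 89.4% at 98.1%, and with no missed case it shrinks to the single point 100%. But the formula is used for planning, and the *Statistical analysis* section does not commit to it. These figures are only a caution against carrying it forward. Leaving the interval method to an analysis plan is not an error.
- A reader might infer that a rule-out decision flips at 5 missed of 203, where the normal-approximation lower limit is 95.4% and the exact one just under 94.4%. The article has no rule that the lower limit must exceed 95%; it aims to estimate NPV.

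**Conclusion.** The stated precision is wrong as written, to a limited extent. At the planning NPV of 95%, 203 test negatives give about −4/+2.5 points, so the lower arm is about 1 point longer than printed. At about 230 test negatives the excess is 0.6 to 0.7 point. The shortfall applies from 95% to about 98%; above that, 203 test negatives keep the lower arm within 3 points.

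The result at 95% needs only the article's n and NPV and a standard binomial interval. The 230 rests on the article's 15% and 10% and on every unaffected child testing negative; fewer test negatives would lengthen the arm. The higher NPVs rest on the cited point estimates and on prevalence at its 15% ceiling.

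This does not show that the study is too small. The article promises no particular lower limit, and the 315 to 319 test negatives for a 3-point lower arm only measure the gap.

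**What to change.** In *Sample size justification* and *NPV Calculation*, replace the ±3% with the interval that the design gives. Suggested wording:

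> With 203 test-negative children and an observed NPV of 95%, the exact 95% confidence interval is about 91% to 98%. With 0, 1, 2 or 4 missed cases, the lower limit is 98.2%, 97.3%, 96.5% or 95.0%.

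Report NPV with a Wilson or Clopper-Pearson interval, so that the analysis matches the restated precision.

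The cost is about two sentences and no extra patients. The only drawback is that the stated precision looks slightly less favourable, with a lower arm of about 4 points instead of 3.

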#### Procalcitonin

0.5 ml of blood is taken from the samples collected as part of routine care. POCT PCT testing is done on this sample in the ED using the Samsung IB-10 analyser with a positive threshold level of > 1.93 ng/ml. If insufficient blood is obtained, then routine testing is prioritised. Routine blood testing includes WBC, CRP, coagulation screen, blood gas, and molecular testing for *N. meningitidis*, human enteroviruses, and other viral and bacterial targets (including *Streptococcus pneumoniae* and *Haemophilus influenzae*) using reference-laboratory real-time PCR methods – Fig. 2.

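### At the protocol's cited test accuracy, 300 recruits give about 170 to 200 children negative on both tests, not the 203 that the sample size section says they achieve

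*Protocol article*

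**What the plan says.** Under Sample size justification, the protocol article says "we need 203 test negative patients (negative LAMP & low procalcitonin"), so the required count is of children negative on both index tests. The purpose is "to estimate a negative predictive value (NPV) of 95% or greater", "with confidence intervals of +/− 3" percentage points. The NPV Calculation section gives the formula and the result, 203.

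Two further inputs follow: a prevalence of at most 15%, and a combined 10% for refused consent and dropout. The conclusion is "We therefore aim to recruit a total of 300 patients to achieve this". The step from 203 to 300 is not shown, and neither section mentions specificity or the share of children expected to be test-negative.

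The accuracy figures are in the background. The Procalcitonin section describes PCT as "specific (0.74 [95%CI 0.4–0.92]) in diagnosing early MD", with sensitivity 0.89. The section on LAMP-MD gives sensitivity 0.89 and specificity 1.0 (95% CI 0.97 to 1.0). The Procalcitonin section on performing the index tests sets the positive threshold at above 1.93 ng/ml and adds: "If insufficient blood is obtained, then routine testing is prioritised".

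**The concern.** The number of children negative on both tests depends on specificity as well as prevalence. Every disease-free child with a raised PCT leaves the group in which the NPV is estimated. At a specificity of 0.74 that is about a quarter of the disease-free children, and the inputs beside the recruitment target make no visible allowance for them.

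This is the article's only sample size justification. The sponsor chose NPV because the clinical emphasis is on ruling out a life-threatening infection, and the limitations section calls the study powered for diagnostic accuracy. A reader will take 203 negatives and ±3 points as what 300 recruits deliver.

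**Working it through.** **Reproducing 203.** With z = 1.96, NPV = 0.95 and W = 0.03:

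1.96² × 0.95 × 0.05 / 0.03² = 202.75, rounded up to 203. The figure reproduces.

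**From 203 to 300 with the two named inputs.** 203 / (0.85 × 0.90) = 265.4, so 266. The target of 300 exceeds this by 34, and the article does not explain the difference.

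**Share required.** After 10% loss, 300 × 0.90 = 270 children remain. Reaching 203 needs 203 / 270 = 75.2% of them to be negative on both tests.

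**Share implied by the cited accuracy.** Inputs: PCT specificity 0.74, LAMP specificity 1.0, both sensitivities 0.89.

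Expected double-negatives = 270 × [(1 − prevalence) × 0.74 × 1.0 + prevalence × m]

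Here m is the share of cases missed by both tests. It is 0.11² = 0.0121 if misses are independent and 0.11 if they overlap fully. The article does not give m, so both ends are assumptions. At 15% prevalence the true negatives are 270 × 0.85 × 0.74 = 169.8, and the false negatives are 270 × 0.15 × m = 0.5 to 4.5.

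The half-width is 1.96 × √(0.0475 / n) at NPV 95%, using the independent-miss count.

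| Prevalence | Double-negatives (independent to fully overlapping misses) | Half-width at NPV 95% |
|---|---|---|
| 15% | 170.3 to 174.3 | ±3.3 points |
| 10% | 180.1 to 182.8 | ±3.2 points |
| 5% | 190.0 to 191.3 | ±3.1 points |
| 0% | 199.8 | ±3.0 points |

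**Sensitivity to PCT specificity, at 15% prevalence with independent misses.**
- Specificity 0.40: 270 × (0.85 × 0.40 + 0.15 × 0.0121) = 92.3, half-width ±4.4 points.
- Specificity 0.92: 270 × (0.85 × 0.92 + 0.15 × 0.0121) = 211.6, half-width ±2.9 points.
- Specificity needed for 203: (203/270 − 0.15 × 0.0121) / 0.85 = 0.88.

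**Recruits needed for 203 at specificity 0.74 and 15% prevalence.** 203 / [0.90 × (0.85 × 0.74 + 0.15 × 0.0121)] gives 358. With fully overlapping misses it is about 350.

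**Precision if the NPV is above 95%.** With 170 negatives and NPV 95.9%, 1.96 × √(0.959 × 0.041 / 170) = 0.0298, just inside ±3 points. The cited sensitivities imply a higher NPV still at 15% prevalence:
- Independent misses: 169.8 / 170.3 = 99.7%, Wald half-width ±0.8 points.
- Fully overlapping misses: 169.8 / 174.3 = 97.4%, half-width ±2.3 points.

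The ±0.8 should not be taken literally, because the Wald formula is unreliable with half an expected false negative.

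**The case against.** Four stronger readings are tempting, and the article does not support them.

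**That specificity was forgotten.** The route to 300 is not shown. If every disease-free child had been treated as test-negative, the answer would have been 266. An unstated allowance cannot be excluded: a 75% test-negative share with 10% loss gives 203 / (0.75 × 0.90) = 301. What stands is that no share is stated, and that 75% is above the 63% (0.85 × 0.74) implied at the 15% ceiling.

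**That the design cannot achieve ±3 points.** The ±3.3 holds only at 15% prevalence and an NPV of exactly 95%. The section plans for 95% or greater, and the cited sensitivities point to about 97% to 99.7%, where the interval is narrower. The count falls short of the stated 203, but the precision goal may well be met.

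**That the shortfall at every prevalence is material.** Near 0% it is about 3 children (200 against 203). If 300 were read as evaluable children, the count would be 300 × (0.85 × 0.74 + 0.15 × 0.0121) = 189 at 15% prevalence, still short, but 211 at 5%, which is enough. Because consent is deferred and children without it are excluded, taking the 10% out of the 300 is the more natural reading.

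**That missing PCT and invalid LAMP results lie outside the 10%.** Dropout is not defined and no rate is given, so the article leaves this open.

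It is also fair to say that 0.74 is a background estimate with a wide interval, is not tied to the 1.93 ng/ml cut-off and is never adopted as a design input. A specificity of 0.88, inside the cited interval, would deliver 203 at 15% prevalence. This limits how firmly 170 can be asserted. It does not supply the missing justification for 203, since 0.74 is the only PCT specificity the article offers.

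**Conclusion.** The point holds as a misstatement of moderate to minor weight. The sample size section says 300 recruits achieve 203 double-negative children. At the article's cited point estimates the expected number is about 170 to 174 at 15% prevalence, rising to about 200 near 0%, so 203 is not reached anywhere in the stated prevalence range. At an NPV of 95% the cost is at most about 0.3 points of half-width at the cited specificity. It could reach ±4.4 points at the lower confidence limit for PCT specificity.

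This rests on 10% being lost from the 300, PCT specificity 0.74, LAMP specificity 1.0 and both sensitivities 0.89. Lowering LAMP specificity to its cited lower limit of 0.97 gives 165 at 15% prevalence. The recruitment target does not have to change.

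**What to change.** Keep 300. State the assumed share of children negative on both tests and its source, and replace the claim that 300 delivers 203. Suggested wording:

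> With 10% loss, PCT specificity 0.74 and LAMP specificity 1.0, we expect about 170 (prevalence 15%) to 200 (prevalence near 0%) children negative on both tests, giving a half-width of about ±3.3 to ±3.0 percentage points at an NPV of 95%. At 15% prevalence the expected number ranges from 92 to 212 for PCT specificity 0.40 to 0.92 (±4.4 to ±2.9 points).

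If the sponsor holds a specificity estimate for the 1.93 ng/ml cut-off, use and cite that value instead and recompute the figures. Also say whether the 10% includes children with too little blood for PCT and those with an invalid LAMP result. If it does not, give an assumed rate.

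The cost is rewording one paragraph. The stated precision becomes slightly less favourable, and no patients or procedures are added.
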